Our planned intention to treat analyses will compare APT against SSMC alone, and both CBT and GET against APT. Assuming α = 5% and a power of 90%, we require a minimum of 135 participants in the SSMC alone and APT groups, 80 participants in the GET group and 40 in the CBT group [46]. However these last two numbers are insufficient to study predictors, process, or cost-effectiveness. We will have low statistical power to detect the difference between CBT and GET, though our estimates will be useful in planning future trials. As an example, to detect a difference in responder rates of 50 and 60%, with 90% power, would require 520 participants per group; numbers beyond a realistic two-arm trial. Therefore, we will study equal numbers of 135 participants in each of the four arms, which gives us greater than 90% power to study differences in efficacy between APT and both CBT and GET. We will adjust our numbers for dropouts, at the same time as designing the trial and its management to minimise dropouts. Dropout rates were 12 and 33% in the two studies of GET [42,43] and 3, 10, and 40% in the three studies of rehabilitative CBT [39-41]. On the basis of our own previous trials we estimate a dropout rate of 10%. We therefore require approximately 150 participants in each intervention group, or 600 participants in all. Calculation of the sample size required to detect economic differences between intervention groups requires data on cost per change in outcome, which are not currently available.

##### 

**Stratification at randomisation** Allocation of interventions to participants was by minimisation with a random component [47] and four stratification factors:

Centre (6 strata): 1 and 4, 2, 3, 5, 6, 7

CDC Criteria (2 strata): Met or unmet

London Criteria (2 strata): Met or unmet

Current Depressive Disorder (2 strata): Present or absent

Participants found to be incorrectly stratified will be kept in their original strata for the primary analysis in accordance with the principle of intention-to-treat (ITT) [48]. The extent of incorrect stratification will be reported.

#### **
*Data collection*
**

##### 

**Screening measures** A clinic patient log book was kept of all new CFS/ME referrals to trial centres to facilitate monitoring of recruitment to the trial. Screening information will not be used in the analysis except for:

1. Reasons for patients not taking part in the trial (see Participant Flow).

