##### **Withdrawals from the trial and losses to follow-up**

The decision to withdraw a participant from follow-up within the trial is made only when the participant withdraws their consent to research follow-up. All reasonable attempts are made to continue to follow up all participants, including those that withdraw from intervention.

For the purposes of analysis, losses to follow-up are those missing all primary outcome scale data at all follow-up assessments, those missing all primary outcome scale data at weeks 24 and 52, or those missing all primary outcome scale data at week 52.

The numbers of withdrawals and losses to follow-up will be reported (see Comparisons of Losses to Follow-Up).

#### **
*Statistical considerations*
**

##### 

**Stratification in the analysis** The primary analysis of therapy effect will be adjusted by the factors used for stratification at randomisation (that is, centre, CDC criteria, London criteria and current depressive disorder) [12,49] and by the baseline assessment of the outcome variable.

##### 

**Method for handling centre effects** The PACE trial was designed with variation in participant outcomes between centres rather than between doctors or therapists in mind. For the primary analysis to be consistent with the trial design, the primary method for handling contextual variation in the analysis of therapy effects will be to include centre as a fixed covariate. The centre that randomises the largest number of participants will be the reference category. The centre assigned to each participant will be based on the participant’s centre at randomisation. Consideration will also be given to including centre as a random effect [50].

##### 

**Method for handling other clustering effects** Outcomes at weeks 12, 24 and 52 are nested within participants. The primary method for handling clustering associated with repeated measurements will be to fit a cluster-specific random effects model [51-53] including the participant as a random intercept, and investigating the addition of a random slope over time. Where therapy effects cannot be interpreted as population-averaged effects because outcomes are binary, a population-average (GEE) model will also be fitted.

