**Method for handling dropouts and missing data** Data are missing completely at random (MCAR) when they represent a simple random sample of the complete sample and the missing data mechanism is independent of all observed and unobserved variables. The assumption that data are missing at random (MAR) is reasonable when missing data represent an identifiable stratified sample of the complete sample and the missing data mechanism is dependent only on other known and observed variables. Data are missing not at random (MNAR) where missing data represent an unidentifiable stratified sample of the complete sample and the missing data mechanism depends on measured and unmeasured variables. The model describing the missing data mechanism will take any clustering effects into consideration. The planned strategy for handling missing data at the item [56] and scale [57] levels will depend on whether the amount of item-missing data observed is minimal. Within practical constraints it will be assumed that data are missing at random (MAR) conditional on the variables included in the substantive model.

##### 

**Missing item data** To ensure the same strategy is followed across all scales reported in the principal paper(s) any guidance given by authors of validated questionnaires will be superseded by the strategy outlined here. Where item-missing data are considered minimal (defined here as no more than 10% of participants with any missing item data across visits where collected or where no more than 20% of the items within a scale are missing within participants), prorating (that is, mean imputation across items within a scale, or subscale where scales are formed of subscales, for each visit and participant) [56] will be used. The focus will instead be on handling scale-missing data. Any bias or underestimation of variance of scores associated with prorating is anticipated to be negligible where item-missing data are minimal [56]. We will report the amount of missing item data by the percentage of participants who have more than 10% item missing data for each scale reported.

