The amount of item-missing data is expected to be minimal. However, if this is not so for any outcome scale then multiple imputation [58,59] at the item-level will be the primary method used. Items will be imputed 100 times [60] separately for each scale (with the exception of the CFQ and SF-36PF, which will be imputed simultaneously). All of the other items for that scale across all time points (including baseline), scores (overall and any subscales) across all time points (including baseline), the four stratification factors at randomisation, randomised intervention, main therapist, and main SSMC doctor will be included in the imputation model.

##### 

**Missing scale data** Missing baseline scale data are not an issue for the primary analysis of efficacy; no missing data are expected for the stratification factors. Where the CFQ or SF-36PF is missing at baseline they will be replaced by the relevant scale at screening. There is specific guidance for missing baseline scale data, and this will be followed [61]. That is, we will use mean imputation of baseline variables assuming baseline and outcome are correlated less than 0.6.

Where the amount of item-missing data is considered minimal, missing outcome scale-data will be handled within the primary analysis by maximum likelihood [57,62] under a similar model for the missing data mechanism assumed for missing item data (see section above). We will report the amount of missing scale data by the percentage of participants who have more than 10% missing item data for each scale reported.

##### **
*Loss to follow-up*
**

Some participants will withdraw from follow-up during the trial, and for these it may be more appropriate to assume data are missing not at random (MNAR). Where more than 10% of randomised participants are lost to follow-up, the impact of this will be investigated in a sensitivity analysis using the weighting approach described by Carpenter, Kenward and White [63] if multiple imputation is the primary method, or comparing selection model and pattern-mixture model therapy effect estimates [64] where maximum likelihood is the primary method.

##### **
*Method for handling multiple comparisons and multiplicity*
**

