##### **Baseline adjustment**

By design factors only

Not applicable

By design factors and additional factors

This is the primary analysis.

##### 

**Model assumption checks** The following assumptions will be checked:

1. Independence of residuals will be checked using the supportive analyses described in Method for Handling Other Clustering Effects section. ICC and within-cluster variance estimates will be reported.

2. Distribution of residuals and random effects will be checked visually using Q-Q plots and histograms of the residuals and by plotting the between-participant variation in participant outcomes and where appropriate the between-centre, the within-doctor but between-interventions, and the between-therapist variation in participant outcomes. Deviations from a Normal distribution would indicate a violation of model assumptions. In this event an alternative approach to the analysis would be investigated.

3. Equal variance of residuals will be checked visually using plots of the standardised residuals against the predicted values.

4. Absence of an intervention-by-centre interaction will be checked in the primary analysis by including fixed contrasts for the intervention-by-centre interaction.

Checks will be made for extreme outliers and points with high leverage. In the event that these are found, the analysis will be reported with and without these observations together with any relevant details.

##### 

**Other analyses supporting the primary analysis** A number of sensitivity analyses will be employed to examine the robustness of the conclusions of the primary analysis to:

1. Categorical responder/improver analysis.

Clinically significant improvement will be taken as a CGI participant score of 1 (very much improved) or 2 (much improved). CGI (P) scores of 3 (a little improved), 4 (no change) and 5 (a little worse) will be considered as non-improvement. CGI (P) scores of 6 (much worse) and 7 (very much worse) will be considered as deterioration. The primary analyses will be repeated replacing the primary outcomes with the CGI (P) (response versus no response versus deterioration) and using mixed-effects logistic regression.

2. Methods for handling missing data.

The primary analysis will be repeated assuming data are missing not at random (MNAR) as described in Method for Handling Dropouts and Missing Data section.

3. Choice of sample.

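### The plan's only MNAR sensitivity analysis depends on pooled loss above 10%, a threshold equal to the planned dropout allowance and blind to loss by arm

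*SAP article*

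**What the plan says.** All references are to the SAP article.

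- *Method for handling dropouts and missing data*: for the main analysis, "it will be assumed that data are missing at random (MAR) conditional on the variables included in the substantive model".
- *Loss to follow-up*, in the same section: of participants who withdraw from follow-up, "for these it may be more appropriate to assume data are missing not at random (MNAR"). The next sentence sets the condition: "Where more than 10% of randomised participants are lost to follow-up, the impact of this will be investigated in a sensitivity analysis". The methods named are a weighting approach if multiple imputation is primary, or a comparison of selection and pattern-mixture models if maximum likelihood is primary.
- *Withdrawals from the trial and losses to follow-up*: three alternative definitions of loss, each requiring all primary outcome scale data to be absent. The last is "or those missing all primary outcome scale data at week 52".
- *Sample size calculation taken from the protocol (v5.2)*: "On the basis of our own previous trials we estimate a dropout rate of 10"%. It also cites earlier experience: "Dropout rates were 12 and 33% in the two studies of GET [42,43] and 3, 10, and 40% in the three studies" of CBT.
- *Other analyses supporting the primary analysis*, item 2: "The primary analysis will be repeated assuming data are missing not at random (MNAR) as described in Method for Handling Dropouts and Missing Data section".
- *Description of available data*, *Description of missing data* and *Comparison of losses to follow-up*: availability, reasons for missing data and losses are summarised by intervention, descriptively. None of these is linked to the MNAR analysis.

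**The concern.** The plan names the assumption that may fail for withdrawers, then tests it only above a threshold that attrition at the planned rate would not exceed. The threshold is also applied to the wrong quantity. The primary results are five pairwise contrasts at 52 weeks, and bias in each depends on who is missing from the two arms compared, whereas the trigger looks at the four arms together.

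Participants are unblinded and the primary outcomes are self-rated. The safety definitions also anticipate withdrawal from therapy because of reported worsening, so reasons for leaving could differ by arm. The SAP makes consistency across sensitivity analyses one input to its intervention recommendations (*Method for handling multiple comparisons and multiplicity*). If the MNAR analysis does not run, that input is missing for the missing-data assumption.

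The count that feeds the trigger is also loosely fixed. The rule does not say which definition of loss applies. If the three are read as alternatives, the week 52 definition contains the other two. On the natural reading, a participant with a CFQ but no SF-36PF at week 52 is not counted, although the two outcomes are modelled separately.

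**Working it through.** **Inputs from the SAP.** 135 per arm before dropout, 10% dropout, 150 per arm and 600 in all; 641 randomised; trigger strictly above 10%; 0.5 SD = 8 points and minimal clinically important difference (MCID) = 5 points on SF-36PF. **Assumed here:** independent losses, about 160 per arm (641/4 = 160.25), the arm-specific loss rates, and the size of any departure from MAR.

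**1. The plan's own figure.** 135 / (1 − 0.10) = 150 per arm, and 4 × 150 = 600, as stated. Planned losses are 0.10 × 600 = 60, exactly 10%. Because the rule says more than 10%, 60 of 600 would not fire it.

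**2. The trigger at the number randomised.** 0.10 × 641 = 64.1. So 64 losses (64/641 = 9.98%) do not fire it and 65 (10.14%) do.

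**3. Chance that no MNAR analysis is run.** P(X ≤ 64) for X ~ Binomial(641, p):

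| True loss p | P(no MNAR analysis) |
|---|---|
| 8% | 0.970 |
| 9% | 0.827 |
| 10% | 0.528 |
| 11% | 0.226 |
| 12% | 0.063 |

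With 600 randomised, the value at 10% is 0.534.

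**4. Unequal loss that stays under the trigger.** Losses of 24, 8, 16 and 16 in arms of 160 are 15%, 5%, 10% and 10%. The total is 24 + 8 + 16 + 16 = 64, so the trigger does not fire. A more extreme split, 8 in each of three arms and 40 in the fourth (5% and 25%), also totals 64.

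**5. What this could do to a contrast.** Let π be the proportion lost in an arm and δ the amount by which the lost are truly worse than MAR predicts. The bias in the contrast of arms 1 and 0 is π₁δ₁ − π₀δ₀. The SD is 8/0.5 = 16 points on SF-36PF.

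| Loss, arm 1 v arm 0 | Departure from MAR | Bias (SF-36PF points) | Share of 5-point MCID |
|---|---|---|---|
| 10% v 10% | same δ in both arms | 0 | 0% |
| 15% v 10% | 1 SD in both | (0.15 − 0.10) × 16 = 0.8 | 16% |
| 15% v 5% | 1 SD in both | (0.15 − 0.05) × 16 = 1.6 | 32% |
| 15%, any comparator | 0.5 SD in arm 1 only | 0.15 × 8 = 1.2 | 24% |
| 15%, any comparator | 1 SD in arm 1 only | 0.15 × 16 = 2.4 | 48% |

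**The case against.** The best counter-argument is that item 2 of the sensitivity list already commits to the MNAR repeat and carries no threshold; its cross-reference could be to the method alone. That reading is possible. But the section it points to attaches the condition to the analysis itself, so the condition most naturally carries over. If the authors meant otherwise, the two places conflict. Either way they must be reconciled.

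It can also be said that scaling sensitivity work to the amount of missing data is a transparent, prespecified rule, and that small losses do little harm. This stands for small and balanced loss. A pooled 10% does not guarantee balance.

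Three further inferences go beyond the documents:

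- A reader might infer that without the trigger nothing checks MAR. The SAP plans to examine associations between missingness and potential predictors, and to report losses and reasons by intervention. Imbalance would be visible. What is missing is its effect on the contrasts.
- A reader might infer that imbalance switches the analysis off. It does not: unequal loss totalling more than 10% still fires the rule. The rule is merely insensitive to arm.
- A reader might infer that attrition at the planned rate itself biases the result. With equal loss and equal shifts the contrast is unbiased.

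The sample-size section does not define dropout, so equating it with loss to follow-up is an assumption. The earlier dropout rates cut both ways: they make unequal loss plausible, but also loss well above 10%, where the analysis would very probably run. The documents give no indication of how often one primary scale would be missing without the other.

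**Conclusion.** The concern holds as a weakness in a prespecified rule, not as evidence of bias. The only MNAR analysis is tied to a pooled threshold equal to the dropout allowance. At a true loss of 10% it is about as likely as not to be skipped; at 8% it almost certainly is, and at 12% it almost certainly runs. Arm losses of 15% v 5% can pass without it.

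The plausible consequence on SF-36PF, for the 15%, 5%, 10% and 10% pattern, is a bias of about 0 to 2.4 points against an MCID of 5. The upper end is near a worst case, since it needs a full SD departure in one arm and none in the comparator. These figures rest on independent losses, about 160 per arm, an SD of 16 taken from the SAP's own conversion, and assumed shifts. This is worth correcting because the correction is cheap and protects the five primary contrasts.

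**What to change.** In *Loss to follow-up*, delete the 10% condition so that the MNAR analysis listed under *Other analyses supporting the primary analysis* is always run, and align the two wordings. Run it separately for CFQ and SF-36PF, counting missingness per outcome at week 52. Within the pattern-mixture approach already named for the maximum-likelihood route, let the departure from MAR differ by arm, for example by reporting each of the five contrasts over a stated range of δ in each arm. If multiple imputation becomes the primary method, allow arm-specific departures there too.

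The cost is revised wording and a modest amount of extra analysis for each primary outcome. No new data are needed.

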**Figure 3 F3:**
[figure not shown]
CONSORT flow diagram.

Any participant attending at least one session of SSMC or at least one session of APT, CBT, or GET will be regarded as having initiated their randomised intervention. The overall definition of departures from randomised intervention policy (see Departures from Randomised Intervention Policy) will be used to define an inadequate randomised intervention.

##### 

**Representativeness of sample** This will be presented within the baseline comparability tables (see Baseline Comparability of Randomised Groups).

##### 

**Baseline comparability of randomised groups** The following participant-level baseline variables will be summarised both overall and between randomised interventions:

i) Oxford criteria met (yes; no)

ii) Centre (Barts, Bristol, Edinburgh, Kings, Oxford, Royal Free)

iii) Diagnostic criteria (neither met; CDC met only; London met only; both met)

iv) Current depressive disorder (present or absent)

v) GAD (yes, no)

vi) Agoraphobia (yes, no)

vii) Panic disorder (yes, no)

viii) Fibromyalgia (met, unmet)

ix) Duration of CFS/ME since start of illness

x) Taking hypnotics, analgesics or antidepressants

xi) Number of other medications/treatments taken

xii) CFQ Score (continuous)

xiii) SF-36PF score

xiv) Age at randomisation (years) (continuous)

xv) Age at randomisation (years) (18 to 29; 30 to 39; 40 to 49; 50 to 59; 60+)

xvi) Sex (male; female)

xvii) Ethnicity (white; other, unless ‘other’ can be split further)

xviii) Marital status (married and co-habiting, single, divorced/separated/widowed)

xix) Group membership (none; self-help only; national only; both)

xx) Employment status

xxi) Health care costs

xxii) Social care costs

xxiii) Cost of lost employment

Eyeball comparisons of distributions will be carried out as a measure of the randomisation integrity.

The following therapist-level baseline variables will be summarised overall:

i) Primary professional healthcare qualification

ii) Number of calendar years between gaining primary professional healthcare qualification and start date in PACE

iii) Worked in CFS/ME or chronic pain service previously

iv) Employment grade (for health economic analysis)

Doctor variables will be summarised by:

i) Discipline (for example, psychiatrist/physician/GP)

ii) Grade (for example, Consultant/SpR/SHO)

Numbers (with percentages) for binary and categorical variables, and ordered categories plus means (and standard deviations), or medians (with lower and upper quartiles) for continuous variables will be presented. No statistical significance tests or CIs will be calculated for differences between randomised interventions on any participant-level baseline variables [69-71]. Differences in therapist-level baseline variables are expected because therapist characteristics are a component of the randomised intervention policies.

Median (lower and upper quartile) of number of participants per therapist will be reported.

##### 

**Comparison of losses to follow-up** Losses to follow-up will be reported at 13, 26, and 52 weeks by intervention and centre. Narrative summaries will be given of the reasons when known.

##### 

**Therapy and other treatment received** Summaries will be given of treatment received under the intervention policies; these will include:

i) SSMC and APT/CBT/GET received

a. Median (lower and upper quartile, minimum and maximum) number of SSMC sessions attended

a. Median (lower and upper quartile, minimum and maximum) number of APT/CBT/GET sessions attended

ii) Median (lower and upper quartile, minimum and maximum) of proportion of telephone sessions per participant

iii) Patterns of concomitant medications and treatments received - number (proportion) of participants taking hypnotics, analgesics, antidepressants (all as classified by BNF), non-pharmacological treatments, complementary and alternative medicines, up to 52 weeks.

The number and percentage of those who comply will be reported by randomised intervention within the CONSORT diagram. In addition, more detailed descriptions will be given by randomised intervention including:

i) Number (percentage) of participants attending (i) fewer than three sessions of SSMC or (ii) fewer than ten sessions of APT, CBT or GET.

ii) Number and percentage of participants initiating a trial therapy other than the one randomised.

iii) Number, percentage and details of participants receiving a trial intervention from (i) more than one therapist/doctor, (ii) a therapist/doctor from a different centre, or (iii) a therapist delivering their second therapy type.

Details of the following will be reported overall and by randomised intervention:

a) Mid-trial modifications to trial interventions and manuals.

b) Partial suspension of randomisation.

Narrative summaries will be given of the reasons for withdrawal when known.

Each primary outcome will be tabulated in a 2 × 4 table by compliance status and randomised intervention.

##### 

**Unblinding of randomised intervention** While this trial is not blinded, due to impracticability, a number of steps were taken to minimise bias arising from this. The apparent success of these steps will be assessed where possible:

1. Extent of any unblinding of the Trial Steering and Data Monitoring Committees or the blinded statisticians will be reported.

2. Extent of primary outcomes data collected over the phone will be reported by randomised intervention.

3. The degree of self-declared expectations of the trial outcome among the trial team by professional role (that is, SSMC doctor, APT/CBT/GET therapist, therapy leader, centre leader, research staff) and centre by randomised intervention was collected.

4. Participant preferences will be reported by randomised intervention.

5. Participant expectations of outcome will be reported by randomised intervention.

6. Proportion and type of discrepancies between preferred intervention and randomised intervention will be reported by randomised intervention.

#### **
*Interim analyses and safety monitoring analyses*
**

No interim analyses were planned or have been carried out.

#### **
*Analysis of fatigue and disability (co-primary outcomes)*
**

